#### Study design

The study is a cluster-randomized, non-inferiority trial with secondary schools as the unit of randomization. It is designed as a Hybrid Trial Type 2 Effectiveness-Implementation study [10] to answer two key overarching policy-relevant questions: 1) Do either of the CyberRwanda versions (self-service, facilitated) improve the health and wellbeing of youth compared to schools without access to CyberRwanda? and 2) If one or more of the CyberRwanda versions is found to be effective, is the self-service version at least as effective, within a specified margin, as the facilitated version?

In addition to rigorously measuring the impact of CyberRwanda, we will also include data collection beyond the primary outcomes to learn about acceptability, feasibility, and implementation successes and challenges. This will enable the team at the conclusion of the study to understand not only whether CyberRwanda worked, but why and in what context.

The impact evaluation will use an experimental approach embedded in Proctor’s implementation science framework [15]. Should CyberRwanda be found to be effective, the implementation science framework will allow us to determine potential barriers and facilitators to scale-up and sustainability through input from stakeholders at multiple levels: the individual level (students, peer facilitators, parents, and teachers), the organizational level (schools) and the policy level (community leaders, government officials).

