#### Data analysis

To first assess the presence of an intervention effect, we will utilize a generalized linear mixed model (GLMM) with uptake of a modern contraceptive method (binary outcome) and initiation of childbearing (binary outcome) as the outcome variables. The model will include a binary explanatory variable for the intervention group (control vs. CyberRwanda in either the self-service or facilitated arm) with control group as the reference, and model terms for the stratification factor (district) as well as other relevant variables measured at baseline (e.g. age, sex). We will present relative risks and 95% confidence intervals using robust standard errors to account for clustering at the school and district levels.

If there is evidence of a statistically significant intervention effect relative to control, we will proceed with the assessment of non-inferiority to understand whether CyberRwanda self-service is non-inferior to CyberRwanda facilitated within a specified margin. To do this, the coefficients on the categorical variable for the intervention groups can be used as approximations of the log relative risks (RRs) comparing the probability of contraceptive uptake (or initiation of childbearing) in the intervention arms compared to control arm. We will use a one-sided Wald-style test of non-inferiority, based on an a priori specified non-inferiority margin of 50% of the lower bound of the confidence interval for CyberRwanda facilitated.

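### The non-inferiority margin is labelled a priori but is taken from the trial's own facilitated-arm confidence limit, making it too narrow for contraception and too lenient for childbearing

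*Protocol article*

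**What the plan says.** The second of the two policy questions under Study design asks whether, if a version works, "is the self-service version at least as effective, within a specified margin, as the facilitated version". The Data analysis section supplies the rule in three steps.

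- **Gate.** The effect model uses a "binary explanatory variable for the intervention group (control vs. CyberRwanda in either the self-service or facilitated arm"). Then: "If there is evidence of a statistically significant intervention effect relative to control, we will proceed with the assessment of non-inferiority".
- **Scale of the coefficients.** In a model with a categorical arm variable, the arm coefficients are read as approximate log relative risks against control.
- **Test and margin.** "We will use a one-sided Wald-style test of non-inferiority, based on an a priori specified non-inferiority margin of 50% of the lower bound"; the margin in full is "an a priori specified non-inferiority margin of 50% of the lower bound of the confidence interval for CyberRwanda facilitated".

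The same sentences cover contraceptive uptake and initiation of childbearing. The only confidence level given is in "We will present relative risks and 95% confidence intervals using robust standard errors". The section gives no number for the margin, no scale for the 50%, and no source for the interval other than the model just described.

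**The concern.** A margin is the loss of effect one is prepared to accept, and its value should not move with the trial's luck or precision. Here the value is unknown until endline. For contraception, a noisier trial (higher ICC, more attrition) pulls the facilitated lower limit towards no effect and shrinks the margin, just when the standard error of the comparison grows. If the lower limit reaches RR 1, nothing is left to halve, and the pooled gate does not rule this out.

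For childbearing the direction is reversed. Benefit means RR below 1, so the lower limit exaggerates the facilitated effect, and a noisier trial gets a wider margin.

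Self-service versus facilitated is the comparison that makes this a non-inferiority trial. As written, failure on contraception would say little about whether the versions differ, and success on childbearing would be weak evidence that they do not.

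**Working it through.** **Inputs from the protocol article.** Contraceptive use 2% in control and 5% with facilitated (RR 2.5); 60 schools and 50 girls per school; 10% attrition, so 45 girls per school; 95% intervals.

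**Assumed, because not stated.** 20 schools per arm (n = 900 girls per arm); log RR scale for the margin; margin entered in the Wald test as if known; one-sided 5%; ICC 0 to 0.02.

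**The plan's own figure.** The stated 80% power is for the presence of an effect; none is stated for non-inferiority. A two-proportion calculation of 2% versus 5%, with n divided by the design effect, gives 93–96% for facilitated versus control without clustering. It falls to 80% at an ICC of about 0.012 (45 girls) to 0.014 (50 girls). For pooled versus control, 80% is reached at about 0.021–0.024. The plan's 80% is therefore plausible, and ICC 0.012 serves as the planning case.

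**Contraception, identical versions at RR 2.5.** Let b_F and b_S be the log RRs against control. With D = 1 + 44 × ICC, each arm's variance is (1 − p)/(np) × D. At ICC 0, v_c = 0.98/18 = 0.0544 and v_F = v_S = 0.95/45 = 0.0211. Also log 2.5 = 0.916.

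- SE_F = √(v_c + v_F), for facilitated versus control
- SE_D = √(v_F + v_S), for self-service versus facilitated
- SE_R = √(v_S + 0.25 v_F + 0.25 v_c), for b_S − 0.5 b_F
- Expected margin M = 0.5 × (0.916 − 1.96 SE_F)
- Written rule: declare if b_S − b_F + 0.5(b_F − 1.96 SE_F) > 1.645 SE_D, which has probability Φ((M − 1.645 SE_D)/SE_R)

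| | ICC 0 | ICC 0.012 | ICC 0.02 |
|---|---|---|---|
| D | 1.00 | 1.528 | 1.88 |
| SE_F | 0.275 | 0.340 | 0.377 |
| SE_D | 0.205 | 0.254 | 0.282 |
| SE_R | 0.200 | 0.247 | 0.274 |
| M | 0.189 | 0.125 | 0.089 |
| Written rule declares non-inferiority | 23% | 12% | 9% |
| Margin held fixed at M: Φ((M − 1.645 SE_D)/SE_D) | 23% | 13% | 9% |
| Half-retention contrast, gated on facilitated vs control | 70% | 48% | 39% |
| Facilitated lower limit ≤ RR 1: Φ(1.96 − 0.916/SE_F) | 8% | 23% | 32% |
| The same, with the pooled gate passed | 4% | 8% | 9% |

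At ICC 0 the written rule gives (0.189 − 0.338)/0.200 = −0.75, and Φ(−0.75) = 0.23. The last row is a bivariate normal probability that takes the pooled effect as (b_F + b_S)/2 with variance v_c + (v_F + v_S)/4. The third and second rows from the top of the results show that fixing the margin at its expected value changes almost nothing. At one-sided 2.5% the written rule gives 14% at ICC 0 and 7% at ICC 0.01.

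**Childbearing, literal lower bound.** The margin is 0.5 × (|log RR| + 1.96 SE_F). Illustration with assumed control rate 10%, RR 0.6, 900 per arm and ICC 0.01: SE_F = 0.199, so the expected margin is 0.5 × (0.511 + 0.389) = 0.450, against a full facilitated effect of 0.511. If self-service keeps half the log effect, SE_D = 0.210 and SE_R = 0.170. The pass probability is Φ((0.98 × 0.199 − 1.645 × 0.210)/0.170) = Φ(−0.89), about 19%. Over control rates 5–20% and RR 0.5–0.75 it is about 17–20%. All three standard errors scale together, so sample size and ICC barely affect it. Among trials that pass the pooled gate it is 18–45% (ICC 0.01).

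**The case against.** **The formula is pre-stated even if the value is not.** True, and a rule fixed beforehand is better than a margin chosen afterwards. But Study design promises a specified margin, and a formula whose result depends on the trial's precision does not provide one. A reader might infer that the interval comes from earlier data; the article names none.

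**The randomness of the margin is not the problem.** This stands. A reader might point to the 0.2% pass rate when self-service keeps exactly half the log effect (against 5% for the retention contrast) and conclude that treating a random margin as fixed wrecks the error rate. That boundary belongs to the contrast, not to the written rule. At the rule's own expected boundary, retention of about 79–90% of the log effect, it rejects about 4.6% at a nominal 5%. For contraception the rule is strict and does not inflate false claims.

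**Non-inferiority is not out of reach.** A reader might infer that it could hardly ever be shown. The figures do not support that: 23% at ICC 0 for RR 2.5, and at ICC 0.01 28%, 64% and 88% for RR 3, 4 and 5. Sample size also plays a part: a margin fixed at 0.5 × 0.916 = 0.458 reaches only 58% at ICC 0.01.

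**The 8–32% is not all a cost of the rule.** A facilitated lower limit at or below RR 1 means facilitated versus control is not significant, and the remedy would stop there too. What is specific to the plan is that its pooled gate can let such trials through to a test without a margin.

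**Scale, one-sided level and standard error may be in an analysis plan not shown.** Their absence is not the point here. The numbers do depend on them: at ICC 0.01 other scale readings pass identical versions 51% or 99.9% of the time, and the latter also passes half-effect versions 85% of the time.

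**Conclusion.** The point holds and should be settled before endline data are seen. The margin is not fixed in advance, it moves with precision, and the single wording cannot serve two outcomes whose benefits run in opposite directions. For contraception the lower-bound discount leaves about 9–23% power for identical versions at the design effect, mainly because the margin is narrow. For childbearing the literal wording is too lenient, passing half-effect versions at about 17–20% or more against a nominal 5%. It would be wrong to describe the rule as conservative throughout.

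These sizes rest on the log RR reading, 20 schools per arm, 900 participants per arm, one-sided 5%, ICC 0–0.02, and assumed childbearing rates. The label and direction faults do not depend on the ICC, the level or the rates.

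**What to change.** Remove the a priori label from a data-derived margin and choose one of two routes.

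1. **Retention test.** Pre-state the fraction to be kept, for example the 50% already in the text. From the model with the three-category arm variable, test b_S − 0.5 b_F > 0 for contraception and < 0 for childbearing. Take the standard error from the joint covariance matrix, state the one-sided level, and proceed only after facilitated versus control is significant.
2. **Fixed margin.** State a number and its scale for each outcome before endline data.

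Either way, report the retained fraction with its confidence interval and the power of the non-inferiority test.

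The cost is protocol and analysis-plan wording plus one contrast from the same model and data, but it is not purely editorial. The retention fraction becomes an explicit choice that is more lenient for contraception than the written rule, and it needs justification. The gate moves from pooled CyberRwanda to facilitated versus control, which changes the testing hierarchy. Power for identical versions is still only about 40–70%, and the report should say so.

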CyberRwanda is a digital intervention for urban and peri-urban youth aged 12–19. Designed in partnership with youth and their communities, it combines age-appropriate storytelling content about FP/RH and economic empowerment, with discreet, streamlined access to contraception and other essential products from trained pharmacists through a mobile ordering platform. Through CyberRwanda, young people can order products online for discreet in-person collection at participating pharmacies, after answering medically-relevant questions and reading information about the products online. All participating pharmacies are trained on the provision of youth-friendly care. CyberRwanda addresses the challenges adolescents face in finding and accessing accurate information on socially taboo topics, locating youth-friendly care, and then discreetly ordering and receiving products. Co-designed with healthcare providers, accompanying training tools for pharmacists support them to provide youth-friendly care.

The objective of CyberRwanda is to improve a spectrum of adolescent health outcomes, with specific focus on increased uptake of modern contraception, delayed initiation of childbearing, and increased rates of HIV testing. Within a Theory of Planned Behavior (TPB) framework [7], we hypothesize that CyberRwanda will strengthen the knowledge, attitudes, perceived social norms, and perceived behavioral control of participants, leading to the aforementioned health outcomes.

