#### Outcomes

The primary outcomes, measured at the individual participant level, are:
Uptake of a modern method of contraception (ages 15–19): The proportion of youth who report currently using a modern method of contraception at endline (24 months)Initiation of childbearing (ages 15–19): The proportion of youth who report having ever been pregnant or fathered a pregnancy at endline (24 months), regardless of the pregnancy outcomeHIV testing (ages 12–19): The proportion of youth who have ever had an HIV test at endline (24 months).

While the intervention will be available to 12–19-year-olds at study intervention schools, the first two primary outcomes are measured for 15–19-year-olds for two main reasons: 1) sample size would need to be increased substantially to have sufficient statistical power to detect an effect in the younger age group; and 2) stakeholders were more comfortable focusing the evaluation outcomes on older adolescents to align with social expectations on talking about sexuality. HIV testing is not as stigmatized according to age, because it is routinely conducted irrespective of sexual activity.

Secondary outcomes include the following, measured at the individual participant level for participants aged 15–19 at endline (24 months):
Level of knowledge of contraceptive methods and how to prevent pregnancyBehavioral intentions to use contraceptives, pregnancy intentions, intent to discuss contraceptives with partnerSelf-efficacy related to family planning and reproductive healthSocial norms related to contraceptive use and other reproductive health behaviorsEngagement in employment, education and training: proportion of youth currently in school, training or employment.

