#### Sample size calculations

The sample size was determined for the primary outcome of uptake of a modern contraceptive method. Power and sample size analyses were conducted for the primary analysis using 2000 simulated datasets (created in R statistical software) constructed based on historic data on the proportion of sexually active youth currently using a modern contraceptive method.

The primary analysis is powered at 80% to detect the presence of an intervention effect when CyberRwanda facilitated has a relative risk of at least 2.5. Although this relative risk seems large, in absolute terms, the baseline percentage of girls using contraception is only 2%, so this would mean increasing that to 5%. To achieve this power, we need to enroll 60 schools and 50 girls per school (equal cluster size is assumed). When we include boys (who are not part of the primary outcome on which the study is powered), this means we will enroll a total of 100 students per school, for a total of 6000 students in the study.

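### The single non-inferiority margin takes the lower confidence bound for childbearing as well, where benefit is RR<1, so it always concedes more than half of the estimated facilitated effect

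*Protocol article*

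**What the plan says.** Under Data analysis, the protocol first tests both CyberRwanda arms together against control. It then states: "If there is evidence of a statistically significant intervention effect relative to control, we will proceed with the assessment of non-inferiority". The second step works with model coefficients read as log relative risks, "comparing the probability of contraceptive uptake (or initiation of childbearing) in the intervention arms compared to control arm", so both outcomes are in scope. The test is a one-sided Wald test "based on an a priori specified non-inferiority margin of 50% of the lower bound of the confidence interval for CyberRwanda facilitated". No separate margin, inverted coding or other bound is given for childbearing.

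Under Outcomes, childbearing is the unwanted event: "The proportion of youth who report having ever been pregnant or fathered a pregnancy at endline". The Background gives the aims as "increased uptake of modern contraception, delayed initiation of childbearing, and increased rates of HIV testing". Benefit is therefore RR<1 for childbearing. For contraception it is RR>1, and Sample size calculations powers the trial for the case "when CyberRwanda facilitated has a relative risk of at least 2.5".

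**The concern.** A margin built from half of a confidence bound is cautious only if the bound is the one nearest no effect. For contraception the lower bound is that one. For childbearing it is the opposite end, the largest benefit the data allow, so the 50% in the rule no longer means that half of the effect is kept.

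Whether self-service is as effective as facilitated, within a margin, is one of the two policy questions under Study design, and childbearing is a primary outcome. A margin that is too lenient there could support the lighter model when it keeps less than half of the facilitated benefit.

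**Working it through.** **Inputs from the protocol.** The margin rule, the log-RR scale, the 95% intervals, the pooled gate and the direction of benefit for each outcome. No numerical margin is stated, so there is none to reproduce. The 80% power figure concerns contraception. Without clustering, 2% versus 5% needs 588 girls per arm. With 900 per arm (20 schools × 45) that corresponds to an ICC of about 0.012, since 900/(1 + 44 × 0.012) = 589. The protocol gives no ICC, and nothing below depends on this figure.

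**Algebra (no assumed rates).** Let b be the facilitated log-RR against control, se its standard error and z = |b|/se. For childbearing b < 0, so the lower bound is −(|b| + 1.96se) and the margin is

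M = (|b| + 1.96se)/2.

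- M > |b|/2 always, because se > 0.
- M ≥ |b| exactly when 1.96se ≥ |b|, that is z ≤ 1.96.
- M is at least the effect assured by the bound nearest zero, |b| − 1.96se, when 3 × 1.96se ≥ |b|, that is z ≤ 5.88.
- M increases with se.

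**Illustration: childbearing, facilitated RR 0.50 (|b| = 0.693; assumed).**

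| z | 95% CI | M as written | Share of point effect | Self-service RR at the margin | Half of the bound nearest 1 |
|---|---|---|---|---|---|
| 3 | 0.32–0.79 | 0.573 | 83% | 0.89 | 0.120 (17%) |
| 2.5 | 0.29–0.86 | 0.618 | 89% | 0.93 | 0.075 (11%) |
| 1.96 | 0.25–1.00 | 0.693 | 100% | 1.00 | 0 |
| 1.5 | 0.20–1.24 | 0.80 | 115% | 1.11 | none: the bound has crossed 1 |

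The fifth column is 0.50 × exp(M). For example, exp(0.618) = 1.86 and 0.50 × 1.86 = 0.93. For contraception at RR 2.5 and z = 2.5 (CI 1.22–5.13), the same rule gives 0.5 × ln 1.22 = 0.099, or 11% of ln 2.5 = 0.916. At equal z the rule is strict for one outcome and lenient for the other.

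**Role of the gate.** It tests the two CyberRwanda arms pooled against control. Facilitated need not be significant alone, so the last two rows can occur in a trial that reaches the non-inferiority step.

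**Simulation (assumed inputs).** Beta-binomial data with 20 schools per arm, 45 students per school, control risk 5–15%, ICC 0.01–0.02, facilitated RR 0.6, one-sided 5%, school-level robust variance and 20,000 replicates. The results are the share of all trials that pass the gate and are declared non-inferior:

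- Self-service RR 0.8, which keeps ln 0.8/ln 0.6 = 0.223/0.511 = 44% of the log effect: about 8–12% as written, about 3% with a direct 50%-retention test, and 0.1–0.2% with the bound nearest 1.
- Self-service RR 1.0 (no effect): about 0.2–1.6% as written.
- Self-service RR 0.6 (equally effective): 28–77% as written, 15–51% with the retention test, and 2–11% with the bound nearest 1.

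**The case against.** The margin is not the decision threshold. The confidence limit for self-service against facilitated must clear it. Take the z = 2.5 row and assume the same se (0.277) for that contrast. The observed log ratio must then be below 0.618 − 1.645 × 0.277 = 0.162, so the observed self-service RR must be below 0.50 × exp(0.162) = 0.59, not 0.93. This stands. A reader might infer from the margin that a useless self-service arm would often be declared non-inferior. The simulation does not support that, with under 2% of trials.

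A reader might also infer that the margin generally gives away the whole facilitated point effect. It does so only when facilitated is not clearly significant on its own (z ≤ 1.96). The gate permits that, but it is not the general case.

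The protocol gives no childbearing rate, RR, ICC or one-sided alpha. The 45 per school is the 50 girls of the contraception calculation less 10% attrition, whereas childbearing is counted in both sexes at ages 15–19. The percentages are therefore illustrations.

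Finally, the sentence may have been written with contraception in mind, and a full analysis plan may word it by outcome. That is possible, but childbearing is named in the sentence before the margin, and nothing in the article limits the rule to contraception. The log scale for the 50% is inferred from that same sentence. On the raw scale, half of an RR below 1 would not be a usable margin either.

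**Conclusion.** The rule is wrong as written for childbearing. That follows from the direction of benefit and the algebra alone: the nominal 50% is never preserved, and the margin rewards imprecision. The practical size rests on the assumed inputs. It is a roughly three- to fourfold higher chance of accepting an arm that keeps 44% of the log effect (about 8–12% against about 3%). The documents do not support a claim that self-service could routinely pass with little or no benefit. The contraception margin has its bound on the correct side and is not affected.

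**What to change.** State the rule by direction of benefit before endline data are analysed. Preferred: for childbearing, declare self-service non-inferior if the upper one-sided confidence limit of β_self − 0.5 × β_facilitated is below zero, with the variance taken from the model's covariance matrix. Alternative: define the margin as half of the log-RR bound nearest RR = 1, which is the lower bound for contraception and the upper bound for childbearing. In either case, run the test only if facilitated itself differs significantly from control in the beneficial direction, because otherwise there is no established effect to retain.

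The change is a sentence or two and needs no extra data, but it costs power, as the equal-effectiveness results above show. The nearest-bound margin would seldom succeed at this sample size, which is why the retention contrast is preferred. Requiring facilitated to be significant alone can only lower those rates further, since they were computed with the pooled gate.
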